### Sample size and power

2.4

As part of Aim 1 and to reach enrollment goals, we plan to screen at least 220 individuals for elevated BNP levels, identifying people who use methamphetamine at risk for heart failure. This estimate reflects an initial screening target; however, the study is powered on the number of individuals who screen positive rather than the total number screened, and screening will continue as needed to enroll 122 participants with elevated BNP. We will continue screening as needed to reach our target enrollment. No prior study has reported the prevalence of positive screening (using BNP) for heart failure in community-dwelling people who use methamphetamine who are not already diagnosed with cardiomyopathy, however one prior cohort study with people who use methamphetamine presenting to the emergency department found that 63 % had abnormal BNP levels (Richards et al., 2018), which likely overestimates the prevalence in a community-dwelling population. In contrast, in the STOP-HF randomized controlled trial, approximately 40 % of community-dwelling primary care patients with cardiovascular risk factors had a BNP > 50 (Ledwidge et al., 2013), providing a more conservative reference point for BNP positivity in non-acute settings. Based on these findings, we anticipate that 122 individuals from those will have elevated BNP levels indicative of possible heart failure and meet other eligibility criteria, making them eligible for enrollment in the Aim 2 randomized controlled trial. Assuming a 10 % linkage to cardiology care in the enhanced usual care (EUC) arm, a sample size of 122 participants allows us to detect a clinically meaningful difference in linkage rates between study arms with adequate statistical power. So based on these considerations, this sample sizeallows detection of a 20 % increase in the linkage to cardiology care in the telecardiology arm (i.e., achieving a rate of 30 % at 2 months), assuming 80 % power for a two-sided test of proportions at α= 0.05. This baseline estimate is informed by linkage rates reported in symptomatic, hospitalized populations, which may differ significantly from outpatient screening populations, in whom follow-up care rates are expected to be lower.

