#### Secondary outcomes

2.8.2

Secondary outcomes include participants’ reported changes in confidence and knowledge of MAHF-associated heart failure risk, severity of heart failure symptoms, and adherence to GDMT.

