### Analysis

2.9

#### Aim 1

2.9.1

We assess acceptability by determining what proportion of peers can conduct the screening outreach intervention; we will assess fidelity based on which aspects of screening were completed. During audit and feedback meetings with peers, we will assess ease and barriers to implementing the screening as intended. We will descriptively examine patterns of reach and acceptability within the rural population served.

As part of the implementation evaluation of Aim 1, clinic study investigators will review positive screens and subsequent testing results (i.e., echocardiography has been performed, and whether the echocardiogram reveals structural heart disease).

#### Aim 2

2.9.2

We hypothesize that participants assigned to the intervention group will experience a higher proportion of linkage to cardiology care at 2-months (primary outcome). We will test statistical imbalance between the intervention and control groups on baseline demographic characteristics; those showing significant imbalance will be included as covariates in the primary outcome model. Linkage to cardiology care at 2-months, the primary outcome, will be analyzed with a generalized estimating equation (GEE) model with binomial family and logit link, which allows us to control correlation introduced by peer site. Missing data is imputed as not retained, and robust standard errors will be used for hypothesis tests.

Secondary outcomes will be tested using GEE models with appropriate distributions and link functions; we test hypotheses of within- and between-group changes over time (screening, 2, and 6 months), comparing the intervention to EUC. Missing secondary outcome data will be handled using multiple imputations if missing at random is a reasonable assumption, single imputation if missing not at random. Sensitivity analyses will be carried out to evaluate the impact of missing data.

Details on the sample size justification, including assumptions about baseline rates and detectable effect sizes, are provided in Section 2.4. Sample size and power.

#### Aim 3

2.9.3

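### Single imputation is assigned to secondary outcomes judged missing not at random; it does not in itself model that mechanism, and it can understate standard errors

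*Protocol article*

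**What the plan says.** Section 2.8.2 lists the secondary outcomes as "participants’ reported changes in confidence and knowledge of MAHF-associated heart failure risk, severity of heart failure symptoms, and adherence to GDMT". Section 2.9.2 states the model: "Secondary outcomes will be tested using GEE models with appropriate distributions and link functions". It covers three time points: "we test hypotheses of within- and between-group changes over time (screening, 2, and 6 months), comparing the intervention to EUC".

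For missing values in these outcomes, section 2.9.2 makes the method depend on the judged mechanism: "multiple imputations if missing at random is a reasonable assumption, single imputation if missing not at random". The next sentence adds: "Sensitivity analyses will be carried out to evaluate the impact of missing data". The article does not say which single value would be filled in, what departure from missing at random (MAR) it would represent, or how the standard error would allow for filled-in values.

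The primary outcome has its own rule in the preceding paragraph: "Missing data is imputed as not retained, and robust standard errors will be used for hypothesis tests".

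**The concern.** The rule pairs a mechanism with a method that does not address it. Handling MNAR needs an explicit assumption about how unseen values depart from what the observed data predict: a shift, a pattern-mixture or reference-based rule, or a selection model. The word single supplies none of these.

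The switch also depends on a distinction that the observed data cannot settle. MAR and MNAR models can fit the observed values equally well, so the main method for a secondary outcome rests on an unverifiable judgement.

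Finally, the rule can run the wrong way. Where missingness is judged benign, multiple imputation carries the imputation uncertainty into the confidence interval. Where it is judged serious, a single filled-in value may drop that uncertainty. At stake are the confidence intervals and tests for symptom severity, knowledge and confidence, and adherence. These are participant-reported at 2 and 6 months, so a participant who is not reached leaves a missing value.

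**Working it through.** **Inputs**
- Imputation rule: section 2.9.2, quoted above.
- Total sample size 122: section 2.4. A 1:1 split (61 per arm) is an assumption, since the article does not state the ratio.
- Missing fraction m: not in the article. 20–30% is assumed, with 10–40% as the wider range.
- Fill-in method: not in the article. Arm mean, one random draw and a fixed value are compared.

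**The plan's own figure.** The article gives no figure for missing secondary data. Its one design figure is the sample size for the primary outcome, which serves here only to set the arm size. With 10% and 30% linkage, two-sided α = 0.05 and 80% power, the pooled formula gives per arm:

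(1.96 × √(2 × 0.20 × 0.80) + 0.842 × √(0.10 × 0.90 + 0.30 × 0.70))² / 0.20² = (1.109 + 0.461)² / 0.04 ≈ 61.6, so 62 per arm or 124 in total.

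At 61 per arm the power is 79.6%. The stated 122 reproduces to within two participants.

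**Arm-mean fill-in** (continuous outcome with variance σ², n per arm, missing at random):
- True variance of the difference between arms: 2σ² / [n(1 − m)].
- Variance the analysis reports: about 2(1 − m)σ² / n.
- Naive SE / true SE = 1 − m. Type I error = 2[1 − Φ(1.96(1 − m))].
- m = 20%: ratio 0.80, 1.96 × 0.80 = 1.568, type I error 11.7%.
- m = 30%: ratio 0.70, 1.96 × 0.70 = 1.372, type I error 17.0%.

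**One random draw:**
- True variance: (2σ² / n) × [1/(1 − m) + m]. Reported variance: 2σ² / n.
- m = 20%: 1.25 + 0.20 = 1.45, ratio 1/√1.45 = 0.83, type I error 10.4%.
- m = 30%: 1.429 + 0.30 = 1.729, ratio 1/√1.729 = 0.76, type I error 13.6%.

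**Simulation check** (61 per arm, SD 1, no true effect, 4,000 runs per cell; the fixed value is 1 SD below the mean). Cells show naive SE / true SE, then type I error.

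| Missingness | m | Arm mean | One draw | Fixed value |
|---|---|---|---|---|
| Random | 10% | 0.90, 8.2% | 0.92, 7.4% | 1.01, 5.1% |
| Random | 20% | 0.80, 11.8% | 0.82, 11.4% | 1.00, 5.1% |
| Random | 30% | 0.71, 17.1% | 0.75, 14.3% | 1.00, 5.3% |
| Random | 40% | 0.60, 25.0% | 0.69, 17.6% | 1.01, 5.0% |
| Value-dependent | 10% | 0.87, 9.0% | 0.85, 9.8% | 0.99, 5.7% |
| Value-dependent | 20% | 0.75, 14.9% | 0.80, 11.8% | 1.00, 5.6% |
| Value-dependent | 30% | 0.66, 20.7% | 0.73, 15.2% | 0.98, 5.8% |
| Value-dependent | 40% | 0.57, 26.3% | 0.68, 18.3% | 1.00, 5.6% |

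In the value-dependent rows, lower outcomes are more likely to be missing (log-odds slope 1 per SD, the same in both arms), and m is the missing probability at the mean outcome. Under random missingness at 20% and 30%, the simulation agrees with the formulas to within about one percentage point. Value-dependent missingness gives similar or worse results for the mean and the draw.

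Robust standard errors in the GEE would not repair this, because they treat filled-in values as observed. In section 2.9.2 they are mentioned only in the primary-outcome sentence.

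**The case against.** The strongest reply is that single imputation covers more than a mean or a draw. Filling in a fixed unfavourable value is also single imputation, and it is a crude but explicit MNAR assumption. It is also the only imputation that the article spells out, in the primary-outcome rule. The table shows that it leaves the standard error about right and the type I error at 5–6% in this null setting. This stands. A reader might infer that single imputation always shrinks the standard error, or that 10–17% is the error rate of the plan as written. The article supports neither, because it does not name the fill-in. The reply does not rescue the rule, however. No fixed value is stated for the secondary outcomes, and such a value would test an outcome redefined by it.

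Second, sensitivity analyses for missing data are promised, and their detail may properly sit in a full protocol or SAP that is not shown. This also stands, so it would be wrong to say that none is planned. But sensitivity analyses leave the main rule in place, and that rule is stated here rather than deferred.

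Third, a reader might infer that the branch is chosen after the data are seen, outcome by outcome. The text does not say when or for what unit the judgement is made. What holds is only that the data cannot verify it.

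Fourth, imputing every secondary outcome would be wrong. Section 2.7.1 links the start of guideline-directed medical therapy (GDMT) to reduced ejection fraction. For a participant never prescribed GDMT, adherence is undefined rather than missing. This is right and limits the fix.

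**Conclusion.** The point holds in a conditional form. The rule assigns to MNAR a method that does not in itself model MNAR, and it selects that method on an assumption that the observed data cannot verify. If the fill-in is an arm mean or one random draw treated as observed, standard errors are too small. At 20–30% missing they are about 0.70–0.83 of the correct value, and a nominal 5% test has a type I error of about 10–17%. At 10% missing, the simulated error under random missingness is still 7–8%.

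These figures rest on assumed missing fractions, assumed fill-in methods, a 1:1 split and a simple two-arm continuous outcome at one time point. An imputation that used earlier measurements on the same participant would lose less information, and the understatement would be smaller. The figures measure only the standard-error fault. Any bias from missingness that differs between arms comes on top.

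Only secondary outcomes are affected. The primary outcome and the sample size do not depend on this rule. The change is worth making but does not threaten the main comparison.

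**What to change.** In section 2.9.2, and in the SAP if it repeats the rule:

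1. Delete the single-imputation branch.
2. Make multiple imputation under MAR the main method for secondary outcomes that are defined but missing, done by arm and using baseline and earlier follow-up values. Exclude GDMT adherence in participants never prescribed GDMT.
3. Specify the promised sensitivity analyses as delta-adjusted (pattern-mixture) or tipping-point multiple imputation. Possible MNAR is then examined by varying a stated departure from MAR, and no one has to decide which mechanism holds.

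The cost is a few sentences, a little more programming and somewhat wider confidence intervals. Trial conduct, data collection, sample size and the primary analysis do not change.

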### Study incentives

2.10

Participants will receive up to $120 cash for participating in this study. Anyone who completes the screening assessments will be compensated $5. Those who screen positive and enroll in the study will be compensated $20 for the baseline survey, $30 for the 2-month survey, and $30 for the 6-month survey. Participants invited to participate in the qualitative interviews will receive an additional $40 following the interview. Cash is the preferred and most practical compensation, as few participants have access to transportation to travel to the nearest gift card vendor in this rural area.

### Ethics and dissemination

2.11

The study has been reviewed and approved by the Oregon Health & Science University IRB (IRB#26150). Participant data will be collected and managed using REDCap, a web-based application designed to support data confidentiality. Participant information will be anonymized and assigned unique study identifiers to protect personal identities and will be de-identified and stored in encrypted databases, accessible only to authorized research personnel. In addition, a Certificate of Confidentiality was obtained to further protect sensitive participant information from compelled disclosure. Any breaches of confidentiality will be reported immediately to the IRB and other appropriate authorities.

## Discussion

3

This study represents the first effort to assess the feasibility and acceptability of peer-assisted point-of-care screening and linkage to telecardiology for people who use methamphetamine and are at risk of heart failure in a rural setting. By integrating peers into intervention, we aim to overcome key barriers such as stigma and mistrust, providing holistic, trauma-informed, and accessible support while facilitating timely screening and connection to cardiology care (Kane et al., 2024, Spencer et al., 2024, Avalone et al., 2024, Harris et al., 2022). Additionally, by facilitating screening more quickly than conventional medical clinics, this approach allows for expanded reach, linking more individuals to specialized care. Connecting people at risk to MAHF with cardiology specialists via telehealth helps to alleviate the shortage of resources, facilities, and professionals in rural areas. Peer-assisted treatment ensures better patient engagement and provides a sustainable approach to treatment, as peers can guide and assist patients in navigating the healthcare system, which they are often unfamiliar with, ultimately improving the continuity and quality of care (Jack et al., 2018).

Telehealth, particularly telecardiology, offers significant advantages for rural populations with limited access to healthcare resources and specialized professionals. It allows patients to receive timely consultations and follow-up care without the need for long-distance travel, a critical benefit for those in remote areas (Benavides-Vaello et al., 2013). Telehealth has shown promise in managing chronic conditions like heart failure (Mohammadzadeh et al., 2022) and improving access to addiction treatment, as demonstrated by successful programs such as Peer Assisted Telemedicine for Hepatitis C and Syphilis (PATHS) (Spencer et al., 2024). When paired with peer support, as in our study, telecardiology can broaden reach, enhance trust and engagement, improve linkage to cardiology for individuals who might otherwise avoid treatment, addressing acceptability concerns for stigmatized populations (Sakakibara et al., 2019, Su and Yu, 2019). We anticipate that this model will result in a higher proportion of individuals being connected to cardiology services within two months compared to enhanced usual care. Focus on MAHF is especially relevant, as early identification and intervention are critical to improving outcomes in this high-risk population (Breier et al., 2023, Dickson et al., 2021). Peer-assisted telecardiology also presents a scalable and sustainable care model that could be adapted and implemented in other rural or resource-limited settings, potentially transforming access to specialty care for vulnerable populations (Mahalwar et al., 2023, Sakakibara et al., 2019, Su and Yu, 2019).

If effective, the peer-assisted telehealth approach could be expanded to other communities partnering with local peer organizations and scaled to other chronic conditions and rural areas, offering a replicable framework for integrating telehealth with peer support across diverse healthcare landscapes (Ashford et al., 2018, Bazzi et al., 2024, Spencer et al., 2024). Additionally, this model holds potential for reducing healthcare disparities in marginalized populations, while improving access to specialist care and mitigating the impact of geographic and social isolation (Watson et al., 2022). Furthermore, the peer assisted screening protocol for individuals at risk of MAHF could be adapted in urban settings faced with similarly high rates of MAU.

To our knowledge, this is the first study to assess BNP screening for heart failure risk among community-dwelling people who use methamphetamine. Previous studies focused on emergency or inpatient populations, which likely overestimate prevalence. These community-based estimates provide a novel contribution to guide early identification and linkage to cardiology care.

This study has several limitations that may impact its findings and generalizability. Firstly, the lack of a double-blind design could influence participant responses and potentially lead to expectancy bias, affecting the validity of the results. Additionally, the reliance on peer facilitators for screening and intervention may introduce variability in the quality and consistency of care provided, as potential biases could arise from the peer-selection process, with volunteers possibly not representing the broader population.

## Conclusion

4

The PEER-Heart study addresses a critical gap in the early detection and treatment of methamphetamine-associated heart failure (MAHF) by implementing a novel, scalable model that combines peer-assisted screening with telecardiology. In the context of rising MAU and limited access to specialty care, particularly in rural areas, this intervention seeks to overcome structural barriers such as stigma, transportation, and healthcare shortages. By embedding peers in the care pathway, the study enhances trust, improves participation among people who might otherwise avoid medical services, and facilitates timely linkage to cardiology care. Preliminary findings will inform broader implementation across rural health systems with the aim of improving outcomes and reducing hospitalizations and mortality related to MAHF.

The study contributes a replicable implementation framework for peer-supported telehealth interventions that can be adapted to other chronic conditions and underserved populations. Its emphasis on community engagement, equity, and sustainability offers important guidance for health systems designing care models in low-resource settings. However, successful scale-up will require a responsive care system that ensures fidelity in peer-delivered services and fosters strong collaboration between peers and clinical staff (Scannell, 2021, Scott Kruse et al., 2018). PEER-Heart findings have the potential to shape future telehealth strategies that advance access, equity, and continuity of care in hard-to-reach populations.
